#### Confidentiality {27}

Participation in this study involves the potential risks of accidental breach of confidentiality of the recorded information and breach of the privacy of the participants. This will be minimised by removing direct participant identifiers (i.e. names, Medicare numbers, medical record numbers) from the information stored for the study and used for analysis, securing, and limiting access to linking codes assigned to the study information and limiting access to the information contained within the study to authorised research staff.

#### Plans for collection, laboratory evaluation and storage of biological specimens for genetic or molecular analysis in this trial/future use {33}

The collection, laboratory evaluation and storage of biological specimens for analysis from participants in the PICOBOO trial are outlined in the PICOBOO Laboratory Appendix, relevant SSP and the trial standard operating procedures (SOPs). Blood and saliva samples will be collected at pre-specified time points. Blood will be separated into the sera, plasma, and peripheral blood mononuclear cells (PBMCs) at local sites prior to transportation to reference laboratories for processing. Granulocytes collected from baseline blood samples during gradient centrifugation will be used for deoxyribonucleic acid (DNA) extraction for human leucocytic antigen (HLA) I and II typing. This will be performed to evaluate susceptibility to and protection from SARS-CoV-2 infection and disease. Genomic DNA will be extracted using commercial kits, harmonised across sites. DNA will be aliquoted and stored as per SOPs.

## Statistical methods

### Statistical methods for primary and secondary outcomes {20a}

A Bayesian three-level hierarchical linear model will be used for the primary analysis as it is anticipated that immune responses may be mutually informative across COVID-19 vaccination dose, age groups and potentially across messenger ribonucleic acid (mRNA) vaccine interventions (Pfizer Comirnaty and Moderna Spikevax). For the first level, information is borrowed across vaccination dose number within age groups, intervention allocation and vaccine history. For the second level, information is borrowed across age groups within intervention allocation and vaccine history. Finally, for the third level, information is borrowed across mRNA vaccine intervention allocation, for the ancestral subtypes only, within vaccine history. The model estimates the posterior distribution of the mean log_10_ anti-spike SARS-CoV-2 IgG antibody against Ancestral SARS-CoV-2 measured ~ 28 days after receipt of the assigned booster COVID-19 vaccine for each intervention and vaccination strategy in each stratum, denoted by vaccine history group and age group.

A detailed description of the statistical methods for this trial is beyond the scope of this document and will be reported separately as a statistical appendix plan. The SAP is available from the corresponding author upon request and will be available on the trial website, once live.

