**Methods:**

The Platform Trial In COVID-19 priming and BOOsting (PICOBOO) is a multi-site, multi-arm, Bayesian, adaptive, randomised controlled platform trial. PICOBOO will expeditiously generate and translate high-quality evidence of the immunogenicity, reactogenicity and cross-protection of different COVID-19 priming and booster vaccination strategies against SARS-CoV-2 and its variants/subvariants, specific to the Australian context. While the platform is designed to be vaccine agnostic, participants will be randomised to one of three vaccines at trial commencement, including Pfizer’s Comirnaty, Moderna’s Spikevax or Novavax’s Nuvaxovid COVID-19 vaccine. The protocol structure specifying PICOBOO is modular and hierarchical. Here, we describe the Core Protocol, which outlines the trial processes applicable to all study participants included in the platform trial.

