#### Intervention description {11a}

Eligible participants will be randomised to undergo COVID-19 vaccination according to the priming or booster vaccination schedule(s) stipulated in the relevant SSP. While the platform is designed to be brand-agnostic, the vaccines that will be evaluated at the commencement of the trial will include Pfizer’s Comirnaty® (Pf), Novavax’s Nuvaxovid® (Nx) and Moderna’s Spikevax® (Mod). If the vaccines studied at the commencement of the trial are superseded by alternatives, such as bivalent vaccines, a decision to substitute the vaccine intervention(s) with newer alternatives may occur, at the discretion of the trial steering committee (TSC). A maximum of three interventions per stratum will be evaluated at any given time.

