### Assignment of interventions: allocation

#### Sequence generation {16a}

A sequence of intervention assignments will be generated by an unblinded trial statistician using random permuted blocks for each stratum using computer software with a validated random number generator and equal allocation for all vaccination interventions. These allocations will be specified in the relevant SSP.

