#### Composition of the data monitoring committee, its role and reporting structure {21a}

A Data and Safety Monitoring Committee (DSMC) will be appointed to provide safety oversight. The DSMC will have an advisory role as outlined in the DSMC Charter. The DSMC will be notified of all SAEs in accordance with the DSMC charter and will undertake a timely review of these as per the Charter. The DSMC will inform the coordinating principal investigator (CPI) immediately to recommend termination of the study if deemed necessary following a serious adverse reaction (SAR). The DSMC will meet at least three times per year to monitor and review accumulating safety reports and will make recommendations to the TSC on whether there are any ethical or safety reasons why the trial should not continue or should be modified prior to continuation. The DSMC will consider:The occurrence and nature of adverse eventsWhether additional information on adverse events is requiredTaking appropriate action where necessary to halt the trialIncidents occurring between meetings that require rapid assessment (e.g. sudden unexpected serious adverse events (SUSARs))

Sequential analyses will be performed on the accumulating trial data for the primary estimand at pre-specified times detailed in the statistical appendix. The results of these analyses will be provided confidentially to the DSMC as an unblinded report, including recommendations to continue or stop recruitment into each stratum depending on whether the precision threshold has been met. All recommendations based on pre-specified criteria in the statistical appendix will be reviewed by the DSMC as specified in the DSMC charter. When a precision threshold is confirmed as having been reached by the DSMC and where no compelling reason exists not to reach a conclusion for a specific stratum or trial overall, a recommendation may be issued for a public disclosure of the result. Following any interim analysis, the DSMC will make recommendations to the CPI on whether there are any ethical or safety reasons why the trial should not continue.

The DSMC may request to be unblinded to the vaccine allocation of individual participants and/or to have blinded or unblinded analyses performed by the unblinded trial statistician.

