This Core Protocol sets out the establishment of the first adaptive platform trial within Australia, and one of the few established platforms internationally, to enable the evaluation of different COVID-19 vaccination strategies, concurrently. It is envisaged that this platform will enable the evaluation of multiple COVID-19 vaccination interventions (e.g. different booster numbers) in various population cohorts and/or subgroups. The use of an adaptive platform design has the benefits of flexibility and efficiency compared to conventional trials. This platform will enable researchers to respond with agility to new policy questions as they arise, including the potential rollout of new vaccine formulations (such as bivalent formulations or vaccines targeted to specific variants) become new VoC arise in Australia, prompting evidence-based changes in strategy.

The overarching PICOBOO platform will facilitate separately funded, nested mechanistic substudies by established research networks, which will benefit from the established governance, research, and analytic personnel, recruiting sites and digital and trial infrastructure. This will allow sharing of resources and cost-savings across multiple distinct but closely related trials, which traditionally would have been conducted sequentially or in parallel, rather than simultaneously. It is envisaged that data collection, endpoints and methods for analysis and reporting of results will be standardised across these nested or closely related projects, where possible.

There are two major advantages in using this trial design and protocol structure. Firstly, borrowing information across statistical models when the treatment effect is similar in different strata will contribute information to inform an estimation of the posterior probability in another stratum. Secondly, this flexible trial structure will enable investigators to respond to new policy questions and vaccination interventions as they arise (for example, the impact of primary vaccination on younger age cohorts).

PICOBOO will establish a national biobank of serum, plasma, PBMCs and saliva for future use by Australian researchers. It will be possible to apply emerging technologies assessing cellular, humoral, and mucosal immunity against existing and future SARS-CoV-2 variants/subvariants using these banked samples.

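### Level three of the primary model borrows between two randomised vaccines, so at small stratum sizes the Pfizer:Moderna ratio depends materially on the prior; report the vaccine contrasts without that level as well

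*Protocol article*

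**What the plan says.** The abstract states that "participants will be randomised to one of three vaccines at trial commencement": Comirnaty, Spikevax and Nuvaxovid. Section {11a} adds "A maximum of three interventions per stratum will be evaluated at any given time", and section {16a} specifies "equal allocation for all vaccination interventions".

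Section {20a} gives a Bayesian three-level hierarchical linear model for log10 anti-spike IgG. Level one borrows across dose number. Level two is described as follows: "For the second level, information is borrowed across age groups within intervention allocation and vaccine history". Level three is the one at issue: "for the third level, information is borrowed across mRNA vaccine intervention allocation, for the ancestral subtypes only, within vaccine history". The reason given there is tentative for this level: responses may be mutually informative across dose and age, and "potentially across messenger ribonucleic acid (mRNA) vaccine interventions (Pfizer Comirnaty and Moderna Spikevax".

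The Discussion presents the advantage in these terms: "borrowing information across statistical models when the treatment effect is similar in different strata will contribute information".

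The primary effect measure in section {12} is the GMC for each intervention in each stratum. Comparison of strategies is a secondary objective in section {7}. Under section {21a} the monitoring committee receives "recommendations to continue or stop recruitment into each stratum depending on whether the precision threshold has been met". The prior, and the exact form of the between-vaccine variance, are left to the statistical appendix.

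**The concern.** Levels one and two borrow across subgroups within a vaccine. Level three borrows across vaccines, which are the randomised treatments. Nuvaxovid stays outside it. The restriction to ancestral subtypes does not appear to take the starting arms out, since the primary endpoint is ancestral IgG and the article mentions bivalent vaccines only as later substitutes.

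A group of two members gives one contrast from which to learn how far members differ. If the level pulls the two mRNA means together and the data say little about how hard to pull, a small reported Pfizer-Moderna difference may partly restate the model's assumption. Policy readers could take it as evidence that the two vaccines are interchangeable.

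**Working it through.** The article states no residual SD, prior or stratum size, so there is no figure of its own to reproduce. The sizes below rest on assumptions.

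**Inputs.** From the article: two vaccines pooled at level three; three vaccines with equal allocation; first analysis at 300 vaccination events (section {21b}), hence 300/3 = 100 per arm over all strata, and fewer per arm within a stratum. Assumed: residual SD s = 0.4 log10; true Pfizer-Moderna difference 0.15 log10 (10^0.15 = 1.41-fold); half-normal prior on the between-vaccine SD τ with scale 0.05 to 0.5; arm means exchangeable around a common mRNA mean.

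**Step 1: shrinkage for a given τ.** With n per arm, the share of the observed difference that is kept is τ²/(τ² + s²/n).
- n = 50: s²/n = 0.16/50 = 0.0032. At τ = 0.05 the share is 0.0025/0.0057 = 0.44; at τ = 0.2 it is 0.04/0.0432 = 0.93.
- n = 100: s²/n = 0.0016. The shares are 0.0025/0.0041 = 0.61 and 0.04/0.0416 = 0.96.

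**Step 2: what the data say about τ.** With two members and a flat prior, the likelihood integrated over τ does not converge: it is 0.83, 1.48, 2.13 and 2.78 up to τ = 1, 10, 100 and 1000. One contrast alone does not bound τ from above, so the prior has to contribute.

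**Step 3: averaging over the posterior of τ and over repeated samples** (true difference 0.15; ranges run from prior scale 0.05 to 0.5):

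| n per arm | Unpooled SE, √(2s²/n) | Expected posterior difference | Attenuation | Coverage of 95% interval |
|---|---|---|---|---|
| 25 | 0.113 | 0.042 to 0.119 | 72% to 21% | 0.69 to 0.95 |
| 50 | 0.080 | 0.066 to 0.128 | 56% to 15% | 0.75 to 0.94 |
| 100 | 0.057 | 0.095 to 0.137 | 37% to about 10% | 0.82 to 0.94 |

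Attenuation is 1 minus the expected difference over 0.15; for example, 1 − 0.066/0.15 = 56%. At 50 per arm the posterior mean of τ runs from 0.05 to 0.27, following the prior.

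**Step 4: larger samples.** At 200 per arm with an observed ratio of 1.5, the share kept is 0.84 to 0.98 over scales 0.05 to 1. The prior matters much less there.

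**Step 5: structure above and below.** If one τ is shared over five vaccine histories (33 per arm, observed ratio 1.25 in each), the share kept at scales 0.05 to 1 is 0.19 to 0.35, against 0.23 to 0.76 with one history. Sensitivity to the prior falls, although the pull remains. With three age groups added (observed ratios 1.3, 1.5 and 1.7; 33 per arm per stratum), the middle stratum keeps 0.70 to 0.94. The lowest can keep up to 1.27, because it is drawn to the cross-age difference and not directly to zero.

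**Step 6: Nuvaxovid contrasts.** Each mRNA mean moves by half of what the difference loses. At 50 per arm this is (0.15 − 0.066)/2 = 0.042 to (0.15 − 0.128)/2 = 0.011 log10, a factor of 1.10 to 1.03, in opposite directions for the two vaccines.

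**Step 7: precision stop.** The posterior SD of an mRNA GMC, relative to no level-three pooling, is 0.90 to 0.99 at 50 per arm and 0.98 to 1.01 at 100 per arm.

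**The case against.** The strongest reply is that this is an ordinary and reasoned bias-variance trade. The borrowing is hedged, restricted to ancestral subtypes and kept within vaccine history. Where the vaccines differ little, it helps. At 50 per arm and scales 0.05 to 0.5, the root mean squared error of the contrast relative to the unpooled estimate is 0.35 to 0.79 when the true difference is 0, and 0.56 to 0.83 when it is 0.05 log10. Coverage at a true difference of 0 is 0.97 or higher. The heavy attenuation needs a tight prior, and the appendix that sets the prior is not shown. The primary measure is the arm GMC, not a contrast. All of this stands, and it rules out asking for level three to be removed from the primary or stopping model.

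A reader might also infer that the prior alone sets the shrinkage because two vaccines cannot identify τ. The documents do not support that. Prior and data act together, and the wording does not settle whether τ is separate for each vaccine history; a shared τ would be partly identified. Nor is the absent prior a fault of the article, which leaves it to the appendix.

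The reply does not remove the narrower point. Section {20a} fixes borrowing between two randomised arms, and the Discussion's argument about strata does not cover it.

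**Conclusion.** The concern holds in limited form. Level three pulls two randomised arms towards each other, and at small stratum sizes the Pfizer:Moderna ratio depends materially on the prior. In the two-arm model the attenuation is about 56% to 15% at 50 per arm and 37% to 10% at 100 per arm. These figures rest on the assumed SD of 0.4, difference of 0.15 log10, prior scales and exchangeable form; they omit the age and dose levels, which dilute the pull.

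It may be tempting to conclude that pooling triggers early stratum stops, or that only the Pfizer-Moderna contrast is affected. Neither follows. The gain in mRNA precision is at most about 10% at 50 per arm when the vaccines truly differ by this much, and nil or nearly so at 100. The Nuvaxovid contrasts shift slightly as well. What remains is a risk of interpretation: similarity of the mRNA vaccines could be reported partly because the model assumed it.

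**What to change.** Keep the three-level model as primary for the GMCs and for the precision threshold. Pre-specify in the statistical appendix that the between-vaccine contrasts (Pfizer:Moderna, and Nuvaxovid against each mRNA vaccine) are also reported from the same model without level three, side by side with the pooled results. State that similarity of the mRNA vaccines will not be concluded unless the unpooled estimate supports it.

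The cost is a short addition to the appendix, one extra model fit per analysis, and wider intervals for the unpooled contrasts. Stopping is unaffected.

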### Interim analyses {21b}

The first analysis will be performed after participants have completed 300 vaccination events and have completed 21–31 days of follow-up post-randomisation, and the results from the batched blood samples are available from the laboratory analysis; thereafter, analyses will be performed after every 150 additional vaccination occasions with available laboratory results for the remainder of the trial, unless otherwise stipulated in the statistical appendix.

### Methods for additional analyses (e.g. subgroup analyses) {20b}

The pre-specified mutually exclusive stratum for the primary and secondary analyses is specified in the relevant SSP.

Any endpoints not defined in the “Outcomes {12}” section will be designated as exploratory.

### Methods in analysis to handle protocol non-adherence and any statistical methods to handle missing data {20c}

Immune responses and reactogenicity to COVID-19 vaccines will be assessed using a treatment policy strategy. Further detail regarding the analytical approach to handling intercurrent events is detailed in the statistical appendix.

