### Outcomes {12}

The primary estimand (inferential target for estimation) for all participants, is defined by:*Study population*: Participants ≥ 6 months of age willing to undergo COVID-19 vaccination with vaccines authorised for use (including emergency use or approved under a clinical trial notification).*Intervention*: Prescription of a COVID-19 vaccination intervention within a stratum, defined in the relevant SSP.*Endpoint*: The amount of binding antibody, measured as the geometric mean concentration of ancestral SARS-CoV-2 anti-spike immunoglobulin G (IgG) ~ 28 days after randomisation.*Primary effect measure*: The geometric mean concentration of ancestral SARS-CoV-2 anti-spike IgG for each intervention in each stratum and separately for each SARS-CoV-2 vaccination intervention, adjusting for any differences in baseline factors between intervention arms that might otherwise confound or reduce the certainty of the treatment effect.*Intercurrent events*: This includes events that occur after randomisation that might confound or otherwise impact the measure of the treatment effect of the intervention. Common anticipated intercurrent events include (i) non-adherence to the allocated intervention due to site procedures or availability; (ii) non-adherence to the allocated intervention due to a serious adverse event (SAE) or perceived clinical indication; (iii) missing blood sample within the appropriate window for endpoint collection, excluding those missed due to adverse events (AE)/SAE but including withdrawals and participants lost to follow-up; (iv) missing blood sample within the appropriate window due to AE/SAE but excluding withdrawals and lost to follow-up; (v) evidence of SARS-CoV-2 infection: rapid antigen test (RAT), polymerase chain reaction (PCR) or anti-nucleocapsid antibody seroconversion between randomisation and day ~ 28; and (vi) evidence of a further SARS-CoV-2 vaccine dose following randomisation. Intercurrent events strategies are beyond the scope of this document and will be published separately in a statistical appendix.

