#### Adverse event reporting and harms {22}

Safety reporting for the trial will commence once the first participant is enrolled and will end once the final study participant has completed their final survey on ~ day 720 (+ 56 days) after randomisation. All SAEs, AESI, medically attended AEs (MAAEs) and AEs resulting in withdrawal occurring from day 0 to day 28 after randomisation will be recorded in the eCRF. From day 29 to day 720 after randomisation, all SAEs, AESIs, MAAEs, and AEs resulting in withdrawal that are found to be related to the study vaccine or study procedures will be reported. After day 28, COVID-19 and associated events will be considered a clinical outcome, not an AESI. In addition, any solicited or unsolicited AE regardless of whether attributed to trial vaccination or not occurring daily during the 7 days after vaccination will also be recorded on the CRF. All solicited AEs that persist beyond day 7 or AEs that result in a participants’ withdrawal from the study at any time will be followed up until a satisfactory resolution occurs, or until a non-study related causality is assigned (if the participant consents to this).

All SAEs must be reported to the sponsor within 24 h of study staff awareness of the SAE. An initial SAE report form will be completed with as much information as is available at the time and signed by the principal investigator or delegate unless otherwise specified in the sponsor SOP. All SUSARs will be reported by the sponsor to the TGA. For fatal and life-threatening SUSARs, this will be done immediately but no later than 7 calendar days after the site study team is first aware of the reaction. Any additional relevant information will be reported within 8 calendar days of the initial report. All other SUSARs will be reported within 15 calendar days of being made aware of the event.

The sponsor is responsible for the ongoing safety evaluation of the investigational product. The sponsor maintains overall responsibility for generating safety communications generated through feedback from the DSMC.

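### Reactogenicity is to be assessed by allocated vaccine only, although departures from allocation are expected; an analysis by vaccine received should be stated alongside it

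*Protocol article*

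**What the plan says.** Section {20c} of the protocol article names one strategy for two kinds of outcome: "Immune responses and reactogenicity to COVID-19 vaccines will be assessed using a treatment policy strategy". The next sentence sends further detail on intercurrent events to the statistical appendix, which is not shown.

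The primary estimand under Outcomes {12} defines the intervention as "Prescription of a COVID-19 vaccination intervention within a stratum", that is, by allocation and not by receipt. In the same place the article states: "Common anticipated intercurrent events include (i) non-adherence to the allocated intervention due to site procedures or availability". The second listed event is "non-adherence to the allocated intervention due to a serious adverse event (SAE) or perceived clinical indication". Neither has a rate attached.

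Secondary objective 2 (Objectives {7}) is a comparison of safety and reactogenicity between booster strategies to day 28. Under Adverse event reporting and harms {22}, solicited and unsolicited events "occurring daily during the 7 days after vaccination will also be recorded on the CRF", so that collection window starts at the injection. No section of the article describes a reactogenicity analysis by vaccine received.

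**The concern.** Reactogenicity is a response to the product injected. A treatment policy strategy uses the outcome whatever happened after randomisation, so each participant stays in the allocated group. That suits a policy question about antibody levels after prescribing a vaccine. It suits less well the question of how often a given product causes reactions.

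Two separate mechanisms are involved. If another vaccine is given, its reactions are attributed to the allocated product. If no vaccine is given and the participant stays in the denominator, the arm's rate is diluted by someone with no exposure; no reactions move to another vaccine. Either way, the by-vaccine rates no longer describe the products. Where the result is dilution, the error is not a cautious one: it makes the more reactogenic vaccine look closer to the others. The article says the evidence is meant to inform immunisation policy, so the by-vaccine rates will be read as properties of the products.

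**Working it through.** **Inputs from the article.** Treatment policy for reactogenicity ({20c}); non-adherence anticipated, with no rate (Outcomes {12}); "equal allocation for all vaccination interventions" (Sequence generation {16a}); "A maximum of three interventions per stratum will be evaluated at any given time" (Intervention description {11a}); no fixed sample size (Sample size {14}). The article gives no reaction rate, crossover rate or power for this outcome, so there is no stated figure to reproduce.

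**Assumptions, not from the article.** True reaction rates of 60% (H), 50% (M) and 40% (L) for three vaccines; 10% background if unvaccinated; affected share q from 1% to 20%. The true H-L difference is therefore 20 points.

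**Formulas for the difference seen by allocation.**
- Two-way swap, share q of each arm: [(1-q)H + qL] - [(1-q)L + qH] = (1-2q)(H-L).
- One-way substitution, share q of arm L given H: H - [(1-q)L + qH] = (1-q)(H-L).
- Equal non-receipt in both arms with the same background rate: (1-q)(H-L).
- Non-receipt in arm L only, background b: H - [(1-q)L + qb].
- Non-receipt in arm H only: [(1-q)H + qb] - L.

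**Results, in percentage points against a true 20.**

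| q | Two-way swap | One-way substitution, or equal non-receipt | Non-receipt, L only | Non-receipt, H only |
|---|---|---|---|---|
| 1% | 19.6 | 19.8 | 20.3 | 19.5 |
| 2% | 19.2 | 19.6 | 20.6 | 19.0 |
| 5% | 18.0 | 19.0 | 21.5 | 17.5 |
| 10% | 16.0 | 18.0 | 23.0 | 15.0 |
| 20% | 12.0 | 16.0 | 26.0 | 10.0 |

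Worked example at q = 10%, two-way swap: arm H reads 0.9 x 60 + 0.1 x 40 = 58%; arm L reads 0.9 x 40 + 0.1 x 60 = 42%; the difference is 16. Non-receipt in L only: 0.9 x 40 + 0.1 x 10 = 37%, and 60 - 37 = 23.

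**Three vaccines.** If 10% of arm M receive L, arm M reads 0.9 x 50 + 0.1 x 40 = 49%. The H-M difference rises from 10 to 11 points while M-L falls from 10 to 9. One substitution pattern can widen one contrast and narrow another.

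**Illustrative power.** For a two-proportion comparison with an assumed 100 per arm, 60% against 40%, power is 81% with no swap, 78% at a 2% two-way swap, 72% at 5% and 62% at 10%. This only gives scale: the trial is Bayesian and fixes no sample size.

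**The case against.** The strongest reply has four parts.

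First, objective 2 compares vaccination strategies, and a comparison by allocation is a legitimate randomised estimand for that. Regrouping by vaccine received can confound the comparison, because one listed reason for non-adherence is a perceived clinical indication, which may be related to reaction risk. This stands. It is why the by-allocation comparison should be kept and not replaced.

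Second, the article leaves intercurrent-event handling to the appendix, which may already contain a by-received summary. This stands in part. Only further detail is deferred in {20c}; the strategy for reactogenicity is named there. The point concerns that stated choice and not the absence of an analysis set from a condensed article.

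Third, the effect may be small. Randomisation takes place on the day of vaccination once eligibility and consent are complete (Concealment mechanism {16b}), and two unblinded staff check and dispense the vaccine (Implementation {16c}). This stands: at a 1% to 2% two-way swap, only 2% to 4% of the difference is lost.

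Fourth, a reader might infer more than the article supports:
- That substitution by another trial vaccine is planned or frequent. The article anticipates non-adherence but does not say what is given instead, and the list it appears in belongs to the antibody estimand.
- That differences always shrink towards zero. The working shows patterns in which they grow.
- That serious events, events of special interest and medically attended events fall under the same rule. The sentence in {20c} names immune responses and reactogenicity only.
- That unvaccinated participants will be counted as reaction-free. Solicited collection starts at vaccination, and the article does not say how such participants enter the denominator.

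**Conclusion.** The concern holds in a limited form. The article assigns reactogenicity to a treatment policy strategy, anticipates departures from allocation and states no analysis by vaccine received. If a different vaccine is given, or if unvaccinated participants remain in the denominator, by-vaccine reactogenicity rates and differences will be distorted. Dilution is the usual direction but not the only one.

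The size cannot be determined from the document. Over an assumed two-way swap of 1% to 10%, a 20-point difference would read 19.6 to 16 points; with non-receipt of 1% to 10% confined to the less reactogenic arm, it would read 20.3 to 23. These figures rest on assumed reaction, background and crossover rates. The change is still worth making, because it is cheap and because secondary objective 2 calls for rates that can be read as belonging to a product.

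**What to change.** In {20c}, keep treatment policy for immune responses, and keep it for reactogenicity with respect to other intercurrent events such as infection or a further dose. Merely deleting reactogenicity from the sentence would leave those events without a stated strategy for that outcome. Then add that:
- reactogenicity is summarised and compared among vaccinated participants, grouped by the vaccine actually received;
- the comparison by allocated vaccine is retained and shown beside it;
- for each arm, the number who did not receive the allocated vaccine is reported, with reasons, separating those given another vaccine from those given none.

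The cost is a short addition to {20c} and a matching analysis set in the statistical appendix. No new data collection should be needed: the procedure for unblinding {17b} already has the vaccinations given during the study entered in the national immunisation record. The drawback is that the by-received grouping is not strictly randomised and may be confounded when the departure had a clinical reason. Showing the by-allocation comparison and the departure counts next to it lets a reader judge how much that matters.
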